## Abstract

**Background:**

Ventilator-acquired pneumonia (VAP) is a common reason for antimicrobial therapy in the intensive care unit (ICU). Biomarker-based diagnostics could improve antimicrobial stewardship through rapid exclusion of VAP. Bronchoalveloar lavage (BAL) fluid biomarkers have previously been shown to allow the exclusion of VAP with high confidence.

**Methods/Design:**

This is a prospective, multi-centre, randomised, controlled trial to determine whether a rapid biomarker-based exclusion of VAP results in fewer antibiotics and improved antimicrobial management. Patients with clinically suspected VAP undergo BAL, and VAP is confirmed by growth of a potential pathogen at > 10^4^ colony-forming units per millilitre (CFU/ml). Patients are randomised 1:1, to either a ‘biomarker-guided recommendation on antibiotics’ in which BAL fluid is tested for IL-1β and IL-8 in addition to routine microbiology testing, or to ‘routine use of antibiotics’ in which BAL undergoes routine microbiology testing only. Clinical teams are blinded to intervention until 6 hours after randomisation, when biomarker results are reported to the clinician. The primary outcome is a change in the frequency distribution of antibiotic-free days (AFD) in the 7 days following BAL. Secondary outcome measures include antibiotic use at 14 and 28 days; ventilator-free days; 28-day mortality and ICU mortality; sequential organ failure assessment (SOFA) at days 3, 7 and 14; duration of stay in critical care and the hospital; antibiotic-associated infections; and antibiotic-resistant pathogen cultures up to hospital discharge, death or 56 days. A healthcare-resource-utilisation analysis will be calculated from the duration of critical care and hospital stay. In addition, safety data will be collected with respect to performing BAL. A sample size of 210 will be required to detect a clinically significant shift in the distribution of AFD towards more patients having fewer antibiotics and therefore more AFD.

**Discussion:**

This trial will test whether a rapid biomarker-based exclusion of VAP results in rapid discontinuation of antibiotics and therefore improves antibiotic management in patients with suspected VAP.

**Trial registration:**

ISRCTN65937227. Registered on 22 August 2013. ClinicalTrials.gov, NCT01972425. Registered on 24 October 2013.

**Electronic supplementary material:**

The online version of this article (doi:10.1186/s13063-016-1442-x) contains supplementary material, which is available to authorized users.

## Background

Patients admitted to the intensive care unit (ICU) constitute a group vulnerable to healthcare-associated infection (HCAI), and consistent with that, antibiotic consumption in the ICU is considerably higher than in other hospital environments [1]. The growing global challenge of antimicrobial-resistance requires improved antibiotic stewardship. This judgment is, however, challenging in critically ill patients in whom clinical signs of infection are non-specific and where the consequences of missing a treatable infection may be significant.

Ventilator-acquired pneumonia (VAP) is a common ICU HCAI and highlights the challenges of antibiotic stewardship. Few clinical features have a specificity of greater than 60 % [2–4], and infection is confirmed in approximately 40 % of patients with suspected VAP [5]. The majority of patients with suspected VAP have antibiotics started at the point of clinical suspicion and de-escalation or discontinuation of antibiotics is possible after 2–3 days, when culture information becomes available. During this period, a significant proportion of patients will receive antibiotics that may not be indicated, and furthermore, if antibiotics are not discontinued in light of negative cultures, a full course of unnecessary antibiotics may be administered.

Addressing limitations in diagnostic methods for infections has the potential to improve antibiotic management by expediting the diagnostic process. Biomarkers of infection can act as rapid surrogate markers. In a recent multi-centre observational study [5], we validated the findings of a single-centre-derivation study [6, 7], showing that bronchoalveolar lavage (BAL) fluid biomarkers could form a reliable test to exclude VAP. Low concentrations of BAL fluid interleukin 1-beta (IL-1β) consistently have a strong negative predictive value (NPV) in both the derivation and validation cohorts. Furthermore, in the validation cohort, a combination of IL-1β and IL-8 could be used as a biomarker test to rule out VAP with high confidence, with a NPV of 1 and a post-test probability of 0 % (95 % confidence interval 0–9.2 %). These biomarkers are measured by cytometric bead array (CBA), which is a multi-plex, flow cytometric application that can be performed in approximately 6 hours, offering the potential for a rapid biomarker-based test in the ICU.

The aim of this randomised trial is to determine if, in adult patients with suspected VAP, the use of the additional rule-out biomarker test will improve antibiotic management and reduce antimicrobial use in comparison to decision making based on microbiology results alone.

## Methods/Design

This protocol outlines a multi-centre, prospective, controlled trial in which patients with suspected VAP are randomised 1:1 to a rapid biomarker-rule-out test in addition to standard care, compared to standard care alone (clinical judgment plus standard microbiological culture). The primary outcome measure is antibiotic-free days (AFD) in the 7 days following BAL. This clinical trial adheres to the Consolidated Standards of Reporting Trials statement (Fig. 1) [8] and principles of Good Clinical Practice.

**Fig. 1 Fig1:**
[figure not shown]
Consolidated Standards of Reporting Trials (CONSORT) 2010 flow diagram

### Study population

Participants are being recruited from the ICUs of 17 National Health Service (NHS) Trusts in the UK, for a total of 22 ICUs. These ICUs cover a broad case mix of medical, surgical and trauma patients, who are representative of current practice across the NHS.

Patients with suspected VAP who are at least 18 years of age, intubated and mechanically ventilated for 48 hours or more are considered eligible for inclusion in the trial. VAP is suspected based on the presence of a new or worsening chest X-ray or computed tomography (CT) changes consistent with pneumonia in the context of at least two of the following: temperature < 35 °C or > 38 °C; a white cell count of < 4 × 10^9^ / L or > 11 × 10^9^ / L; or purulent tracheal secretions [9]. Patients must also be considered suitable for early discontinuation of antibiotics by the clinical team (i.e. have no extra-pulmonary source of infection that mandates the use of continued antibiotics).

Patients are excluded on the basis of previously published criteria [10] that predict poor tolerance of the bronchoscopy and BAL that have been previously applied in our studies [5, 7]. These are: PaO_2_ < 8kPa on a FiO_2_ > 0.7; positive end-expiratory pressure of > 15 cm H_2_O; peak airway pressure > 35 cm H_2_O; heart rate > 140 beats per minute; mean arterial pressure < 65 mmHg; bleeding diathesis including platelet count < 20 × 10^9^/L or international normalised ratio (INR) > 3; poorly controlled intracranial pressure (>20 mmHg); or ICU consultant deems the procedure not to be safe. Patients may only be randomised to the study once (i.e. they are excluded if they have had previous BAL as part of the study). Patients are also excluded if assent/consent is declined.

Co-enrolment is allowed with observational studies. Co-enrolment with interventional studies is allowed following consideration of any scientific or statistical interactions in accordance with current UK recommendations [11].

### Biomarker assay and laboratory set up

The biomarker assay is performed in six NHS or university laboratories that act as testing ‘hubs’. Participating ICUs had to be within an expected travel time of 1.5 hours of a hub. BAL fluid samples are transported to the laboratory on ice immediately after sampling and measurement of BAL fluid IL-1β and IL-8 by cytometric bead array is performed with minimal delay on arrival. IL-1β and IL-8 are combined by logistic regression by the equation, established in the validation study [5]:$$ -2.7385 + 1.4633 \times \log 10\left(1 + \mathrm{I}\mathrm{L}-1\upbeta \right)-0.2721 \times \log 10\left(1 + \mathrm{I}\mathrm{L}-8\right) $$

VAP is excluded if the regression output falls below a defined level (-1.7616).

All equipment, reagents and ongoing maintenance are supplied by the study’s industry partner, Becton Dickinson Biosciences (Franklin Lakes, NJ, USA). Each hub has been issued an Accuri C6 flow cytometer. This is a benchtop flow cytometer designed for its ease of use. The biomarker assay and all Accuri standard operating procedures (SOPs) have been designed such that they can be carried out by healthcare service laboratory technicians with limited flow cytometry experience. Centralised training in the biomarker assay and Accuri C6 was provided by investigators and scientists from Newcastle University and Becton Dickinson.

Accuri quality control tests are performed once a week by each hub, and these data are monitored by the flow cytometry core facility in Newcastle University. Technical support is provided by the investigators at Newcastle University and by Becton Dickinson.

### Intervention

All patients enrolled in the trial have suspected VAP and undergo the same clinical procedures of bronchoscopy and BAL. The BAL is performed according to a previously described SOP [5].

Patients are randomised to have BAL samples analysed by either the biomarker test in addition to semi-quantitative culture (the intervention arm) or semi-quantitative cultures alone (the control arm). The intervention arm is referred to as the ‘biomarker-guided recommendation on antibiotics’ group and the control arm the ‘routine use of antibiotics’ group. All semi-quantitative cultures are performed in a NHS or Public Health England laboratory and handled by a SOP in accordance with the UK Standards for Microbiological Investigation [12]. VAP is confirmed by the widely used threshold of growth of a potential pathogen at > 10^4^ colony-forming units per ml (CFU/ml) [13].

Biomarker results are reported to the clinical team by the technician using a standard script after approximately 6 hours. It is anticipated that all patients would have antibiotics started at the point of suspicion of VAP. In the event of a biomarker result that falls below the cut-off value, the clinical team is advised that VAP is excluded with high confidence and that early discontinuation of antibiotics is advised. If the biomarker value is above the threshold the clinical team is advised that VAP cannot be excluded and that standard care should continue.

### Risk to participants

Patients enrolled in this trial are by definition critically unwell, and minimising the risk to these patients is of paramount importance. BAL is an established and widely used technique for sampling the alveolar regions in ICU patients [13, 14]. Not only do eligibility criteria exclude patients who would poorly tolerate a BAL, but patients can be excluded based on the clinicians’ judgment of the risk profile.

The second consideration of risk is around the early discontinuation of antibiotics. The risk exists that antibiotics may be incorrectly discontinued in the face of undetected infection (i.e. in the setting of a false negative biomarker test). The validation study demonstrated that the threshold for excluding VAP using BAL IL-1β and IL-8 had an NPV of 1 which gives confidence in the test’s performance, but with a 95 % confidence interval of 0.92–1.0 false negatives remaining possible. Decisions around antibiotic prescribing are not dictated by the trial protocol, and these ultimately remain at the discretion of the treating clinician. This allows the clinician to restart antibiotics if it is felt they were discontinued inappropriately. This minimises the risk to patients and also makes the trial more pragmatic, testing its use in ‘real life’ clinical practice.

### Primary outcome and sample size

The primary outcome measure is the frequency distribution of AFD in the 7 days following BAL. This interval was used as this is the average reported duration of antibiotic therapy for suspected VAP in UK practice [15]. For the purposes of study design, AFD can be considered to be an integer value with patients in one of eight categories (0–7 AFD). Fewer days of antibiotic treatment will be detected as an increase in the proportion of patients with higher numbers of AFD and fewer patients having zero AFD. Antimicrobials delivered for prophylaxis will be excluded from analysis.

The sample size is based on the frequency distribution of AFD in the 7 days after BAL in our previous validation study. This baseline distribution of AFD showed a skew towards patients with suspected VAP having few or no AFD (with this effect manifest both in those with ultimately confirmed VAP and those in whom BAL microbiology did not confirm VAP). We modelled changes in the distribution of AFD from baseline to a distribution with more patients having higher numbers of AFD. Table 1 gives examples of the different frequency distributions and their effect sizes. We judged a distribution that equates to effect sizes above 0.07 would represent a clinically important difference. By way of illustration, this would be equivalent to a change from a baseline median of 0 AFD (interquartile range 0–2.5 AFD) to a median of 1.5 AFD (interquartile range 0–3.5 AFD) under biomarker-guided treatment. An effect size of 0.0797 requires 90 patients per trial arm and allowing for a 15 % drop out, the total sample size is 210. This outcome measure and effect size was presented for national stakeholder peer review and judged to be appropriate (UK Critical Care Research Forum, July 2013). Figure 2 illustrates the changes in the AFD distribution between baseline and model 3 from Table 1.

**Table 1 Tab1:** Models of different frequency distribution of AFD. Standard care distribution is based on data obtained from our validation cohort. The different models demonstrate increasing shifts in the frequency distribution towards more AFD in the sample. These distributions are illustrative, and different proportions in each category could give the same effect size. *AFD* antibiotic-free days

	Proportion of AFD (%)									
	0	1	2	3	4	5	6	7	N per arm	Effect size
Standard Care (from validation study)	55	10	10	5	5	5	5	5		
Model 1	40	20	15	5	5	5	5	5	215	0.033
Model 2	35	20	15	10	5	5	5	5	138	0.052
Model 3	30	20	15	10	10	5	5	5	96	0.075
Model 4	25	20	20	10	10	5	5	5	68	0.106

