### Randomisation and blinding

Once consent/assent is obtained, the clinical team informs the laboratory technician who will perform the biomarker test, and the technician then initiates randomisation through the Newcastle Clinical Trials Unit (NCTU). Randomisation is performed using a web-based randomisation service. Patients are randomised to the intervention arm or control arm in a 1:1 ratio by permuted blocks of variable length and stratified by site. The randomisation service generates either an instruction that the patient is randomised to ‘biomarker-guided recommendation on antibiotics: analyse sample on arrival’ or to ‘routine use of antibiotics: do not analyse sample on arrival’. This message is emailed to the technician.

The clinical team is initially blinded to the trial arm since all trial procedures are performed in all participants. Unblinding occurs when the biomarker result is called back to the clinical team after approximately 6 hours. To ensure consistency in unblinding, after this period, the clinical team are also informed if the patient was randomised to the control arm. The technician contacts the clinical team with the results according to local arrangements, which include contacting the on-call ICU consultant, ICU resident or the local principal investigator.

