### Statistical analysis

Baseline clinical data will be compared between trial arms for balance using graphical and summary statistics appropriate for the data type of each variable. No formal tests of equality will be carried out. The primary outcome measure will be analysed by a chi-squared test on a 2 × 8 table of study arm versus AFD categories. Secondary outcome measures will be analysed by fitting appropriate generalised linear models with intervention and centre as covariates. Link functions will be determined by the type of outcome variable. A sub-group analysis for patients with trauma or head injury will be included as will a sub-group analysis based on clinician assessment of likelihood of VAP. Data analysis will be performed on an intention-to-treat basis, although other exploratory analyses including per-protocol analysis will be considered. A per-protocol analysis will be performed excluding patients who were randomised to the biomarker-guided recommendation on antibiotics arm, but who had a technical issue with the assay and therefore defaulted to standard care.

A within-trial cost analysis will be undertaken to assess the hospital resource use from the point of randomisation until hospital discharge or death, whichever occurs first, for a maximum of 56 days. Patient-level hospital resource use will be estimated from length of ICU stay and length of hospital stay. Multiple regression analyses will be performed to examine patient factors, which are potentially associated with costs. The robustness of the results will be evaluated using sensitivity analyses.

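### The trial is sized on an effect (0.0797) above both its own threshold of importance (0.07) and the shift it plots (Model 3, 0.075), so 80% power applies only to the larger effect

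*Protocol article*

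**What the plan says.** All of this is in the protocol article.

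- **Threshold.** Primary outcome and sample size: "We judged a distribution that equates to effect sizes above 0.07 would represent a clinically important difference".
- **Illustration.** The same section describes a move from a median of 0 antibiotic-free days (AFD; quartiles 0 and 2.5) "to a median of 1.5 AFD (interquartile range 0–3.5 AFD) under biomarker-guided treatment". It adds: "Figure 2 illustrates the changes in the AFD distribution between baseline and model 3 from Table 1".
- **Table 1.** The Model 3 row has proportions 30/20/15/10/10/5/5/5%, effect size 0.075 and 96 per arm. The standard care row is 55/10/10/5/5/5/5/5%.
- **Sizing.** "An effect size of 0.0797 requires 90 patients per trial arm", and then "allowing for a 15 % drop out, the total sample size is 210". None of the four models in Table 1 has an effect size of 0.0797.
- **Abstract.** "A sample size of 210 will be required to detect a clinically significant shift in the distribution of AFD".
- **Test and allocation.** The primary outcome is "analysed by a chi-squared test on a 2 × 8 table of study arm versus AFD categories". Allocation is 1:1 (Randomisation and blinding).

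The article gives no significance level or power. The full protocol may do so, and that omission alone is not the point here.

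**The concern.** A reader meets the threshold, the worked illustration and the sample size in consecutive sentences and will naturally take them as one argument: shifts above 0.07 matter, this is what such a shift looks like, and 210 patients suffice to find it. The design effect is in fact larger than both the threshold and the plotted model. Table 1 itself asks for 96 evaluable per arm for Model 3, which is 6 per arm more than the 90 planned.

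What is at stake is the reading of a null primary result. If 210 is taken as adequate for every shift the sponsor calls important, a non-significant test may be read as ruling out shifts between 0.07 and about 0.08, where the type II error is higher than the design figure suggests.

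**Working it through.** **Inputs.** Pearson chi-squared on a 2 × 8 table, so 7 degrees of freedom (Statistical analysis); 1:1 allocation; proportions, effect sizes and n per arm from Table 1; 15% dropout and 210 in total. Assumed: 5% significance and 80% power.

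**1. Reproduce Table 1.** With p1 and p2 the proportions in each AFD category, the effect size is w² = Σ (p1 − p2)² / [2(p1 + p2)]. For Model 3:

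0.0625/1.70 + 0.01/0.60 + 0.0025/0.50 + 0.0025/0.30 + 0.0025/0.30 = 0.0368 + 0.0167 + 0.0050 + 0.0083 + 0.0083 = 0.0751.

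The noncentrality with n per arm is 2n × w². For 7 degrees of freedom at 5%, 80% power needs 14.351, so n = 14.351/(2w²).

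| Model | w² recomputed (stated) | n per arm recomputed (stated) |
|---|---|---|
| 1 | 0.0335 (0.033) | 214.1 (215) |
| 2 | 0.0522 (0.052) | 137.4 (138) |
| 3 | 0.0751 (0.075) | 95.5 (96) |
| 4 | 0.1063 (0.106) | 67.5 (68) |

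For 0.0797, n = 14.351/0.1594 = 90.03, which matches the stated 90. Other pairs do not fit: 90% power at 5% (noncentrality 18.284) would need 114.7 per arm, and 80% power at 1% (19.787) would need 19.787/0.1594 = 124.1.

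**2. Match the illustration to Table 1.** Where a cumulative percentage falls exactly on a quartile, take the midpoint to the next category.

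- Standard care accumulates 55, 65, 75, …: median 0, upper quartile 2.5.
- Model 3 accumulates 30, 50, 65, 75, …: lower quartile 0, median 1.5, upper quartile 3.5.
- Models 1 and 2 have median 1 and Model 4 has median 2, so Model 3 is the only row of the table that fits.

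**3. Power of the planned sample** (noncentral chi-squared, 7 degrees of freedom). Since 210 × 0.85 = 178.5, the 15% loss leaves about 89 per arm.

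| Effect size | 90 per arm | 89 per arm (15% lost) | 105 per arm (none lost) |
|---|---|---|---|
| 0.0797 | 80.0% | 79.5% | 86.7% |
| Model 3 (0.0751) | 77.1% | 76.5% | 84.3% |
| 0.07 | 73.5% | 73.0% | 81.1% |

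A simulation of 100,000 trials under Model 3 at 90 per arm gave 77.9%, close to the approximation.

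**4. Numbers needed for 80% power.**

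- Model 3: 96 per arm, 192 evaluable, 192/0.85 = 226 randomised.
- 0.07: 14.351/0.14 = 102.5, so 103 per arm, 206 evaluable, 206/0.85 = 243 randomised.

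**5. Dropout step.** 180/0.85 = 211.8, so 212 rather than 210. Equivalently, 180 of 210 allows a loss of 30/210 = 14.3%. At 0.0797 this costs about half a percentage point of power.

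**The case against.** The strongest reply is that nothing is contradicted. 0.0797 is above 0.07, a trial may be sized inside its important range rather than at the lower edge, and the section reports that the outcome and effect size went to national stakeholder peer review. The abstract speaks of one significant shift, and 0.0797 is one. Nowhere does the article say that 210 covers every effect from 0.07 upwards. All of this stands.

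The illustration also does not identify Model 3 uniquely. The proportions 29.25/20.75/15/10/10/5/5/5% have the same median and quartiles and an effect size of 0.0394 + 0.0188 + 0.0050 + 0.0083 + 0.0083 = 0.0798. The Table 1 caption warns that its rows are examples and that other proportions can share an effect size. A reader might infer that Model 3 was the declared design target and was then abandoned; the text does not say so. What remains is that Model 3 is the only tabulated row that fits, it is the one plotted, and the distribution actually used is not shown.

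A reader might also infer a calculation error. There is none of consequence: 90 per arm is right for 0.0797, and 210 against 212 is close to rounding.

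Finally, the shortfall depends on the loss. Model 3 keeps 80% power if dropout is at most 18/210 = 8.6%, and 0.07 does if it is at most 4/210 = 1.9%. That is fair, but the sponsor itself plans for 15%.

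**Conclusion.** The point holds as a mismatch in the basis of the sample size. The planned 90 evaluable per arm is 6 short of the article's own tabulated requirement for the shift it plots, and 13 short of what 0.07 would need at the same power. The loss is about 3 percentage points of power at Model 3 and about 6.5 at 0.07, or roughly 3.5 and 7 once the 15% dropout is applied to 210. At 0.07 the type II error is then about 27%, against 20% for the design effect.

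The power figures rest on an inferred 5% level and 80% power. The comparison of 96 with 90 per arm needs no such assumption. It would go too far to say that 210 fails to deliver a promised power: the document attaches its sample size to 0.0797 only, and for that effect it is adequate. Severity is minor to moderate.

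**What to change.** Keep 210 and restate what it provides:

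- State the significance level and power used.
- Say that 80% power applies to 0.0797, and give the power at the other two values. For example: *90 evaluable patients per arm give 80% power at the 5% level for an effect size of 0.0797; power is about 77% for Model 3 and about 73% for an effect size of 0.07.*
- Show the AFD distribution behind 0.0797, as a row in Table 1 or a footnote to it.
- Either state that 210 randomised with 15% dropout leaves about 178 evaluable, or give 212 as the number randomised for 180 evaluable.
- Qualify the abstract's sentence on the sample size by naming the effect it refers to, so that a null result is not read as excluding shifts between 0.07 and 0.08.

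The cost is wording only. Recruitment, the primary test and the sample size are unchanged; the stated power becomes slightly less favourable.
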